### Study design

In order to achieve these objectives the study will employ a controlled study design (A) with a time series analysis (pre-post comparison) on clinic and district level (B) (Fig. 1, Table 2). There is no randomization on practice or patient level. A detailed overview of the endpoints for analysis (A) and (B) can be found in under ‘Outcomes’.

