### Recruitment

Patients will be allocated to either study group based on their GPs. GP practices will be predefined as either control or intervention practice based on their participation in the regional MRE-Network. The intervention group will only contain practices that partake in the MRE-Network Heidenheim, while the control group will include non-participating practices from Heidenheim as well as other districts. With the engagement of the physicians association Heidenheim (Kreisärzteschaft Heidenheim) in the conception of the project, we expect a high acceptance amongst GPs. The recruitment of practices is jointly carried out by the Association of Statutory Health Insurance Physicians Baden-Wuerttemberg (Kassenärztliche Vereinigung Baden-Württemberg) and the physician association Heidenheim.

The intervention phase will stretch over a period of 24 months and is preceded by a 6 months recruitment and preparation phase (also see Fig. 2).

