#### Patient pathway

##### (1) **Study inclusion and risk assessment** (intervention and control group)

All patients, irrespective of risk of S Aureus colonization will be screened for risk of colonization with MRSA according to criteria defined by the Robert-Koch Institute (RKI) in the medical consultation session roughly 5 weeks prior to hospital admission (also see Fig. 4).

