### Statistical analysis

**The primary endpoint** (comparison of colonization rates prior to surgery) will be analysed separately for MRSA and MSSA using logistic regression modelling with GEE (Generalized Estimation Equation) correction to account for potential cluster effects. The power calculation (see section 2) was based on the commonly used significance levels for two-sided chi-square tests. Given the higher prevalence of MSSA, two different levels of significance were chosen for MSSA (0.001) and MRSA (0.049). **Analysis of secondary endpoints** will involve adjustment for covariates such as age and gender using logistic regression modelling with GEE correction. However, the interpretation of local significances is not designed to be strictly confirmatory. Due to the multitude of secondary parameters and the lack of a hierarchical structure, a correction for multiple tests is not necessary. Descriptive analyses are performed following scaling and observed data distribution.

**Qualitative data** from focus groups will be transcribed and then analysed using qualitative content analysis [23]. Data collection will continue until thematic saturation is reached. The resulting category system will help to understand the feasibility of the intervention in daily practice from the perspective of providers in outpatient and hospital care. It will thereby provide additional information to the patient perspective evaluated via questionnaire data. Additionally, all qualitative data systematically collected or observed during the study will be considered as data. This means that not only information from focus groups and questionnaires will be analysed, but also all data documented during hotline calls or observed during site visits. This data will be collected by study personnel in the Heidenheim Clinic via a logbook. Entries of free text will be categorized thematically. Data entries will then be analysed descriptively following observed data distribution. Quantitative analysis will be carried out in Microsoft Excel (Version 2010) und IBM SPSS Statistics (Version 25). For qualitative data analysis MAXQDA (Version 2018) will be used.

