There is a risk of selection bias due to the recruitment of intervention practices via the MRE-Network Heidenheim. Additionally, the local community hospital has been active in MRE-prevention prior to the intervention onset. In order to identify potential (positive) effects of prior efforts, we carry out a time series analysis on a hospital and district level. The successful implementation of patient pathways within the hospital setting has proven to be partly dependent on departmental particularities (i.e. staffing, leadership). Current efforts are made to homogenize processes across all relevant departments. Assessing the feasibility of the novel care pathway in the clinical and outpatient setting will therefore take a central role in the overall evaluation.

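### The primary model names only a cluster correction, and covariate adjustment only for secondary endpoints, although the arms are not randomised

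*Protocol article*

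**What the plan says.** All references are to the protocol article.

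- **Statistical analysis, primary endpoint.** Colonisation at admission "will be analysed separately for MRSA and MSSA using logistic regression modelling with GEE (Generalized Estimation Equation) correction to account for potential cluster effects". No covariate is named.
- **Statistical analysis, secondary endpoints.** Their analysis "will involve adjustment for covariates such as age and gender using logistic regression modelling with GEE correction". The article adds that these results are not meant to be strictly confirmatory.
- **Study design.** "There is no randomization on practice or patient level".
- **Recruitment.** "GP practices will be predefined as either control or intervention practice based on their participation in the regional MRE-Network". Intervention practices all belong to the Heidenheim network, while "the control group will include non-participating practices from Heidenheim as well as other districts".
- **Patient pathway, steps 1 and 2.** Every patient in both arms is assessed against the Robert Koch Institute (RKI) criteria for MRSA risk about 5 weeks before admission. The GP swab in the intervention arm follows about 2 weeks before surgery. Table 3 lists the risk assessment among the clinical data collected.
- **Discussion.** "There is a risk of selection bias due to the recruitment of intervention practices via the MRE-Network Heidenheim". The response offered is a time series on hospital and district level.

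**The concern.** The one analysis with confirmatory status is described with less protection against confounding than the analyses without it. In a randomised trial this would matter little. Here patients enter an arm through their GP's membership of a network whose activities, as the article describes them, include screening patients at risk and decontamination. Control patients may also come from other districts. Differences in age, sex, type of surgery, locality or prior MRSA risk are therefore plausible.

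GEE with a sound variance estimate gives a suitable standard error when patients of one practice resemble each other. It leaves the odds ratio centred on the crude difference between arms, including any part due to case mix. With 13,260 patients, even a small systematic difference can reach significance, or can cancel a real benefit. A variable aimed at MRSA carriage is already recorded before the intervention in both arms, but no model is said to use it.

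**Working it through.** **Inputs from the article.** N = 13,260; two-sided alpha 0.049 for MRSA and 0.001 for MSSA (sum 0.050); population carriage of 1-2% for MRSA and 20-30% for S. aureus (Background).

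**Inputs that are assumed.** Equal arms of 13,260 / 2 = 6,630 (the split is in Fig. 3, not shown); the share of patients at RKI risk; the MRSA rate with and without risk; a 25% MSSA baseline; no true intervention effect.

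**The plan's own figure.** The stated 92% power cannot be reproduced, because the text available gives neither expected rates nor arm sizes. The check below does not depend on it.

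**Formulae.** With share q at risk, and MRSA rates p1 (at risk) and p0 (not at risk), the crude rate in an arm is p = q·p1 + (1 − q)·p0. With d = pC − pI and p̄ their mean:

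- SE0 = √[2·p̄(1 − p̄)/n]
- SE1 = √[(pC(1 − pC) + pI(1 − pI))/n]
- P(reject) = Φ[(d − z·SE0)/SE1] + Φ[(−d − z·SE0)/SE1], with z = 1.969 for MRSA and 3.291 for MSSA

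**Worked MRSA example.** p1 = 4%, p0 = 0.5%, 30% at risk in control and 20% in intervention. pC = 0.30·0.04 + 0.70·0.005 = 0.0155; pI = 0.20·0.04 + 0.80·0.005 = 0.0120. Then d = 0.0035, both SEs are 0.00202, d/SE = 1.73, and P(reject) = Φ(1.73 − 1.97) ≈ 0.41. The crude risk ratio is 0.0120/0.0155 = 0.77 with no intervention effect.

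**MRSA scenarios (nominal 4.9%).** The last column divides n by an assumed design effect of 2.

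| p1 / p0 | At risk, control vs intervention | pC / pI | Crude RR | P(reject), no clustering | P(reject), design effect 2 |
|---|---|---|---|---|---|
| 2% / 1.2% | 30% vs 20% | 1.44% / 1.36% | 0.94 | 6.7% | 5.8% |
| 3% / 1% | 25% vs 20% | 1.50% / 1.40% | 0.93 | 7.6% | 6.2% |
| 4% / 0.5% | 30% vs 25% | 1.55% / 1.375% | 0.89 | 13% | 9% |
| 3% / 1% | 30% vs 20% | 1.60% / 1.40% | 0.88 | 15.5% | 10% |
| 4% / 0.5% | 30% vs 20% | 1.55% / 1.20% | 0.77 | 41% | 23% |

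Simulation (4,000 runs) of the second, third and fifth rows gave 8.0%, 13.6% and 40.1% unadjusted, and 5.1%, 4.8% and 4.8% with a Cochran-Mantel-Haenszel test stratified on risk. The return to about 5% is built in, since risk status is the only confounder simulated.

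**Opposite direction.** If the shares in the last row were reversed, the spurious ratio would be 0.0155/0.0120 = 1.29. A true risk ratio of 0.77 would then appear as 0.77 × 1.29 ≈ 1.0.

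**MSSA (nominal 0.1%).** A baseline difference of 25% vs 24% with no true effect gives d = 0.01, SE = 0.00747, d/SE = 1.34 and P(reject) = Φ(1.34 − 3.29) ≈ 2.5%. With 30% or 70% of patients in the intervention arm it is 1.9-2.0%; with a design effect of 2 and equal arms it is about 1%.

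**The case against.** **Silence in a condensed article.** No sentence says that the primary model is unadjusted, and covariate lists are often left to a full protocol or analysis plan. A reader might infer from the article a decision not to adjust; the text does not establish that. What stands is the contrast: the same paragraph does discuss adjustment and attaches it to the secondary endpoints, which goes beyond ordinary brevity.

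**Other text may cover it.** The subgroup paragraph says that remaining stratifications will be taken into account in the model, and promises sensitivity analyses for primary and secondary findings. This leaves adjustment open, but names no variable and commits the primary model to nothing.

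**The time series.** It is directed at the effect of earlier prevention efforts and is a separate analysis (B). Its listed colonisation data are for MRSA only. It does not adjust the comparison between arms.

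**The scenarios are not evidence of imbalance.** This stands. The documents give neither the strength of the RKI criteria nor the share at risk; the Background itself notes that risk-based screening may miss carriers without a risk profile. The 41% needs an eightfold gradient and a ten-point imbalance, and halves roughly with a design effect of 2.

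**Limits of adjustment.** These stand too. RKI status concerns MRSA and may do little for MSSA. Patient covariates do not reach the admitted source of bias, which is practice membership. The argument is about bias, not precision: in a logistic model, simulation of the 30% vs 20% scenario gave a mean standard error of 0.151 unadjusted and 0.153 adjusted.

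**Conclusion.** The point holds in a limited form. The article names covariate adjustment for the non-confirmatory endpoints and only a cluster correction for the confirmatory one, in a design where the arms are self-selected at practice level. As described, the primary odds ratio would carry any measured case-mix difference, in either direction.

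The size is unknown. Under the stated assumptions (equal arms, no true effect, no clustering), modest gradients or imbalances give an MRSA false-positive rate of about 7-15% against 4.9%; only the strong scenario reaches about 40%. For MSSA, one percentage point at baseline gives about 2.5% against 0.1%. Clustering lowers all of these.

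A reader might go further and conclude that the primary result will be falsely positive, or that adjusting for RKI risk would cure the selection bias. The documents support neither: they report no imbalance, and confounding by network membership would remain after adjustment.

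**What to change.** State under Statistical analysis that both primary GEE models adjust for a short prespecified list of variables, using only values from before any decontamination:

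- age, sex and surgical department;
- district of residence or practice, where both arms are represented (a district supplying only controls cannot inform a within-district comparison);
- RKI risk status, which mainly serves the MRSA model.

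Report the unadjusted GEE as a sensitivity analysis and give a baseline table by arm for these variables. Say plainly that residual confounding by practice network membership remains, and do not present adjustment as a gain in precision.

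**Cost.** A few sentences and no extra patients. Risk status is already collected; the other items are ordinary baseline or practice data. The downside is a few more parameters. At an assumed 1-2% carriage, MRSA carriers number about 0.01 × 13,260 = 133 to 0.02 × 13,260 = 265 before any reduction. Department alone takes several parameters, so the list should stay short and sparse categories should be merged by a rule set in advance.

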### Setting

The study will be carried out in the local clinic in Heidenheim, Baden-Wuerttemberg. Heidenheim has a population of roughly 130,500 inhabitants distributed across elven cities and communities. Being the only hospital in the district, the local community hospital offers treatment to around 90% of local inpatient cases. The largest health insurance companies in the Heidenheim district are the AOK Baden Württemberg (Allgemeine Ortskrankenkasse), AOK-Bayern, BKK (Betriebskrankenkasse) and the IKK (Innungskrankenkasse). All have signed selective agreements (§140SGBV) with the local community hospital allowing the majority of the local population to partake in the study.

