#### Sample size

The sample size was calculated to secure enough power for examining the effect of the intervention for both subgroups (MSSA and MRSA) on colonization status upon hospital admission (primary endpoint). We expect cluster effects to be relatively small as the introduction to decontamination measures will be carried out by link nurses who have received a standardized training. With the expected 13,260 Patients a power of 92% would be achievable, assuming that there are no cluster effects. Although the occurrence of a cluster effect cannot be excluded, we believe that with an eligible patient population of 13,260, potential reductions in power would still fall within an acceptable range (also see Fig. 3).

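### With only tens of intervention practices, an uncorrected GEE test would exceed the 0.001 and 0.049 levels; a small-sample correction suited to the smaller arm is a cheap safeguard

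*Protocol article*

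**What the plan says.** Under Statistical analysis, colonization at admission is compared separately for MRSA and MSSA "using logistic regression modelling with GEE (Generalized Estimation Equation) correction to account for potential cluster effects". MSSA is tested at 0.001 and MRSA at 0.049. The same section adds: "The power calculation (see section 2) was based on the commonly used significance levels for two-sided chi-square tests".

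Under Recruitment, allocation is by practice and not by patient: "GP practices will be predefined as either control or intervention practice based on their participation in the regional MRE-Network". Also, "The intervention group will only contain practices that partake in the MRE-Network Heidenheim", while control practices may come from Heidenheim or from other districts. Study design states that there is no randomisation. Setting gives the size of the catchment: "Heidenheim has a population of roughly 130,500 inhabitants".

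Under Sample size, "With the expected 13,260 Patients a power of 92% would be achievable, assuming that there are no cluster effects". Clustering is addressed in words only: "We expect cluster effects to be relatively small".

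The article gives neither the number of practices nor an intracluster correlation (ICC). It does not name the cluster unit in the model, the variance estimator or the reference distribution.

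**The concern.** GEE is the plan's only statistical protection against clustering, since the power figure assumes none. Its usual sandwich variance is estimated from the scatter between practices. With few practices that variance is biased downwards, and a normal reference ignores how imprecisely it is estimated. Both faults make the test reject too often, and the relative error is largest in the far tail, where MSSA is placed.

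What matters most is the number of practices in the smaller arm. Control practices can be added from other districts, but intervention practices cannot. If the intervention arm has only tens of practices and nothing corrects for it, both confirmatory tests exceed their levels, the intervals are too narrow, and the 0.05 shared between the two tests is not delivered.

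**Working it through.** **Inputs from the article.** 13,260 patients; levels 0.001 and 0.049; allocation by practice; one network and about 130,500 inhabitants for the intervention arm. Background carriage is 20 to 30% for *S. aureus* overall and 1 to 2% for MRSA; 25% and 1.5% are used as stand-ins.

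**Assumptions.** Number of practices, ICC, practice-size coefficient of variation (CV) and arm split are not in the article, so ranges are shown. To illustrate scale only: at an assumed 1,000 to 2,000 inhabitants per GP, the district has about 130,500/2,000 = 65 to 130,500/1,000 = 130 GPs. There are fewer practices where GPs share one, and Heidenheim practices are divided between the arms.

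**1. The plan's own figures.** 0.001 + 0.049 = 0.05, so the split is sound as arithmetic. The 92% power cannot be re-derived from the text, which gives no rates, effect or arm sizes (the sample-size figure is not shown in this copy). As an illustration, MRSA at 1.0% against 0.5% with equal arms at 0.049 gives 91%.

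**2. Closed-form approximation.** If the statistic follows t on K − 2 degrees of freedom (K = total practices) but is compared with a normal critical value, true size = 2·P(t(K−2) > z(1−α/2)), with z = 3.291 for 0.001 and 1.969 for 0.049. This captures the reference-distribution error only.

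**3. Simulation of the full uncorrected test.** Null case, 50,000 runs per cell, beta-binomial practices, independence working correlation, sandwich Wald z-test. Size CV 0 or 0.6; 50% or 70% of practices in the intervention arm; ICC 0 to 0.05 for MSSA and 0 to 0.01 for MRSA. One MRSA cell (CV 0.6, ICC 0.01, 70% split) did not finish and is not in the ranges.

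| K | MSSA, formula | MSSA, simulated | MRSA, formula | MRSA, simulated |
|---|---|---|---|---|
| 20 | 0.0041 | 0.0057–0.018 | 0.065 | 0.078–0.114 |
| 40 | 0.0022 | 0.0030–0.0070 | 0.056 | 0.062–0.082 |
| 60 | 0.0017 | 0.0016–0.0042 | 0.054 | 0.057–0.072 |
| 100 | 0.0014 | 0.0014–0.0029 | 0.052 | 0.052–0.061 |
| 200 | 0.0012 | 0.0009–0.0020 | 0.050 | 0.050–0.056 |

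The Monte Carlo standard error is about 0.00014 at 0.001 and 0.001 at 0.049.

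**4. Few intervention practices, many controls.** 40,000 runs, size CV 0.6, MSSA ICC 0.02, MRSA ICC 0.01, 50% or 70% of patients in the intervention arm.

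| Intervention + control practices | MSSA at 0.001 | MRSA at 0.049 |
|---|---|---|
| 20 + 180 | 0.0042–0.0046 | 0.075–0.078 |
| 30 + 170 | 0.0024–0.0030 | 0.064–0.065 |
| 40 + 160 | 0.0016–0.0024 | 0.061 |
| 100 + 100 | 0.0012–0.0017 | 0.053–0.057 |

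All four rows have 200 practices, so the number in the smaller arm drives the error.

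**5. Why total practices minus 2 is the wrong count.** Take 20 + 180 practices with 13,260/2 = 6,630 patients per arm. The design effect is 1 + [(1 + CV²)·m − 1]·ICC, where m is mean practice size.
- Intervention: m = 6,630/20 = 331.5, giving 1 + (1.36 × 331.5 − 1) × 0.02 = 10.0.
- Control: m = 6,630/180 = 36.8, giving 1 + (1.36 × 36.8 − 1) × 0.02 = 1.98.
- With equal patient numbers the arm variances are in this ratio, so Satterthwaite degrees of freedom are (10.0 + 1.98)² / (10.0²/19 + 1.98²/179) ≈ 27. The simple count gives 200 − 2 = 198.

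**6. Effect on the total.** With sizes of 0.002–0.005 and 0.06–0.08, the excess over nominal is 0.001–0.004 for MSSA and 0.011–0.031 for MRSA. The chance of at least one false rejection is at least the larger size (0.06–0.08) and at most the sum (0.062–0.085).

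**7. Candidate corrections with unbalanced arms.**
- Kauermann-Carroll variance with t(K − 2): MSSA up to 0.0028, MRSA up to 0.062.
- Mancl-DeRouen variance with t(K − 2), 15 + 45 practices: MSSA 0.0018–0.0019.
- Mancl-DeRouen variance with Satterthwaite-type degrees of freedom: MSSA 0.0010–0.0015, MRSA 0.047–0.052. A repeat run (40,000 replicates; 15 + 45 practices and the four splits in step 4; MRSA ICC 0.005 or 0.01) gave 0.0010–0.0018 and 0.048–0.055: close to nominal, not exact.

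**The case against.** The strongest reply is that the article does not contain this error. It says GEE and no more; an uncorrected variance and a normal reference are inferred from silence. A small-sample correction is the kind of detail a journal article leaves to the full protocol or analysis plan, neither of which is shown. This stands. A reader might infer that the plan has committed itself to a test that fails its levels, but the text supports only a conditional statement, and its wording is compatible with the correction proposed here.

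Second, the practice count is nowhere stated, and control practices may come from other districts, so the district's population does not limit the total. This is right for the total but does not remove the concern. Only the control arm can grow in that way, and step 4 shows that extra controls do not cure a small intervention arm. It is also right that near 100 practices per arm little excess remains.

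Third, a reader might take the 0.001 level to be the main problem. In relative terms it suffers most (2 to 5 times nominal), but a true level of 0.002 to 0.005 is still strict, and MRSA accounts for most of the absolute excess. Nor is it right that the number of practices replaces 13,260 as the sample size. With a small ICC, patient numbers still drive precision; the practices determine how well the variance is known.

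Finally, allocation is not randomised and the Discussion concedes possible selection bias, which may matter more than exact test size. That limits the weight of this point but is no reason to leave it.

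**Conclusion.** The concern holds conditionally. If the intervention arm has about 15 to 40 practices and the usual uncorrected sandwich z-test is used, the true size is about 0.002 to 0.005 for MSSA and 0.06 to 0.08 for MRSA, and the 0.05 total is exceeded mainly through MRSA. This rests on assumed ICCs of 0.005 to 0.02, a practice-size CV of 0.6 and background carriage rates. That the intervention arm has only tens of practices is plausible from its single-network, single-district recruitment, but is not stated. With about 100 or more practices per arm the excess is small. The documents do not show that the planned test will fail its levels. They show a design in which the default form of the named method probably would, and a better form is available at little cost. This is an inexpensive improvement, not a demonstrated mistake.

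**What to change.** Keep the GEE logistic model and name the GP practice as the cluster. Base both primary tests and their confidence intervals on a Mancl-DeRouen bias-corrected sandwich variance. Use a t reference whose degrees of freedom reflect the smaller arm (Satterthwaite-type), not total practices minus 2. Report the number of practices per arm alongside the result, so that a reader can judge how much the correction matters. If the full analysis plan already specifies an equivalent correction, nothing need change.

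The cost is a sentence or two of analysis-plan wording, slightly wider intervals, and possibly another package for two models if the software named in the article does not offer these options. Data collection, endpoints and the alpha split stay as they are. The change does not address selection bias from non-randomised allocation.

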## Background

*Staphylococcus aureus* (S Aureus) bacteria are detectable on the skin or mucus membranes of the nasal passage and pharynx in about 20 to 30% of the population [1]. Most of S Aureus isolates exhibit sensitivity to beta-lactam antibiotics (e.g. Methicillin or Oxacillin) and are therefore referred to as methicillin-sensitive S Aureus (MSSA). In contrast, methicillin-resistant S Aureus (MRSA) bacteria are resistant to these antibiotics. MRSA isolates are much rarer than MSSA, only affecting about 1 to 2% of the population in Germany [2].

During surgical interventions both bacterial strains (MSSA and MRSA) can cause infections as they gain access to other organs or tissues. If the infection occurs up to 30 days post-surgery and affects the incision or deep tissue at operating sites they are termed surgical site infections (SSI) [3]. Surgical site infections remain the second most common health-care associated infection (HAI) in Europe and the US [4]. SSIs are associated with prolonged hospital stays, additional physician visits, impairment of the healing process and elevated use of antibiotics [5]. The national guideline by the Robert Koch Institute (RKI) [6] on the prevention of SSI, recommends establishing screening and decontamination procedures for S Aureus, in particular for high risk surgical interventions. While MSSA is increasingly recognized as a risk factor internationally, evidence on the effectiveness of screening and decontamination protocols for MSSA is scarce and it is often not explicitly addressed in national guidelines [5, 6]. Correspondingly, preoperative screening and decontamination efforts in German routine care are targeted at MRSA only. Evidence suggests that decolonization regimes for MSSA can be protective against SSI, particularly since MSSA is a noteworthy contributor to SSI prevalence rates [7, 8].

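### The alpha split between MSSA (0.001) and MRSA (0.049) is valid, but weighted Holm from the same levels would be a free improvement, with a gain the article's figures do not determine

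*Protocol article*

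**What the plan says.** The Statistical analysis section states that the primary endpoint "will be analysed separately for MRSA and MSSA using logistic regression modelling with GEE" correction for clustering. The power calculation "was based on the commonly used significance levels for two-sided chi-square tests". The reason for unequal levels is prevalence: "Given the higher prevalence of MSSA", "two different levels of significance were chosen for MSSA (0.001) and MRSA (0.049"). Nothing is said about what happens to one test once the other has succeeded; a further step is neither stated nor excluded.

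The Sample size section says the calculation was meant "to secure enough power for examining the effect of the intervention for both subgroups (MSSA and MRSA"), and gives one power figure: "With the expected 13,260 Patients a power of 92% would be achievable, assuming that there are no cluster effects". It does not say which of the two tests that figure describes. The readable text gives no effect size, design rates or allocation ratio.

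**The concern.** As written, each strain is judged only at its own level. Suppose MRSA gives p = 0.01 and MSSA gives p = 0.002. MRSA succeeds and MSSA fails, although 5% family-wise control does not require MSSA to fail. Once the MRSA null is rejected, its 0.049 could be passed on.

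The matter is not idle here. The sample size was meant to serve both strains. By the article's own account (Background, Discussion), routine care in Germany addresses MRSA only, and extending screening and remuneration to MSSA depends on these results. The MSSA regimen was largely taken over from the MRSA one for want of a national recommendation (Patient pathway), so its effect is arguably the less certain of the two.

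**Working it through.** **1. The stated rule.** 0.001 + 0.049 = 0.050. The split is a correct weighted Bonferroni rule.

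**2. Weighted Holm.** Reject MRSA at 0.049 or MSSA at 0.001; after either rejection, test the other at 0.05. This is a closed test. The joint null is rejected with probability at most 0.049 + 0.001 = 0.05 under any dependence, and each single null is tested at 0.05. With independent tests the error under the joint null is 1 − 0.951 × 0.999 = 0.04995. Simulation at correlations −0.1, 0 and 0.5 gave 0.0495 to 0.0499. Every rejection under the stated rule is also made under Holm.

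**3. The plan's 92%.** It cannot be strictly reproduced without an effect size and allocation ratio. I used the pooled two-sided chi-square:

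power = Φ((d − z·s0)/s1), with d = p0 − p1, s0 = √[p̄(1 − p̄)(1/n1 + 1/n0)], s1 = √[p1(1 − p1)/n1 + p0(1 − p0)/n0], and n divided by the design effect.

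With N = 13,260, assumed 1:1 allocation and MRSA 1% to 0.5%, power at 0.049 is 91.4%, close to the stated figure. At 0.05 it is 91.6%, so MRSA itself gains about 0.1 to 0.2 points from Holm.

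**4. MSSA power under Holm**, taking the tests as independent:

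P(p < 0.001) + P(MRSA rejected at 0.049) × P(0.001 ≤ p < 0.05).

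**5. Equal relative reductions, sized for 92% MRSA power.** The Background puts S aureus "in about 20 to 30% of the population" and MRSA at 1 to 2%; these are not stated as design rates. With MRSA 1% or 2% and allocation 1:3 to 3:1, 92% MRSA power needs a relative reduction of about 37% to 58%. At those reductions, with MSSA at 18% or 25%, MSSA power at 0.001 is 100.0% for design effects 1, 1.5 and 2, and 94% to 100% at design effect 5. Regain at design effects 1 to 2: 0.0 points.

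**6. Smaller equal reductions, one design effect for both strains (1:1).** MSSA power can now fall, but MRSA is seldom rejected, so little alpha is passed on.

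| Assumption | MSSA power, fixed split | Weighted Holm |
|---|---|---|
| MSSA 25%, MRSA 1%, 15% reduction, design effect 1 | 96.7% | 97.1% |
| MSSA 25%, MRSA 1%, 10% reduction, design effect 1 | 54% | 57% |
| MSSA 20%, MRSA 1%, 30% reduction, design effect 5 | 79.5% | 82.0% |

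Over the grid run (reductions 10% to 50%, design effects 1 to 5) the gain is at most about 5 points.

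**7. Clustering that differs by strain.** For a practice-level standard deviation s on the logit scale, the intracluster correlation is roughly s²p(1 − p), so the common outcome suffers more. Assume s = 0.3, 100 patients per practice and 1:1 allocation.

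- MSSA 20%: 1 + 99 × 0.09 × 0.20 × 0.80 = 2.43.
- MRSA 1%: 1 + 99 × 0.09 × 0.01 × 0.99 = 1.09. MRSA 2%: 1 + 99 × 0.09 × 0.02 × 0.98 = 1.17.
- MSSA 20% to 16%: effective n per arm 6,630/2.4256 = 2,733; s0 = 0.01039, s1 = 0.01038. At 0.001: (0.04 − 3.2905 × 0.01039)/0.01038 = 0.56, power 71.2%. At 0.05: power 97.1%.
- MRSA 2% to 1.6% (power 35.6%): 0.712 + 0.356 × 0.259 = 0.804.
- MRSA 1% to 0.5% (power 89.1%): 0.712 + 0.891 × 0.259 = 0.943, about 94%.

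Range for the last case: 97% to 99.7% with s = 0.2 and 50 per practice; 19% to 60% with s = 0.4 and 200 per practice.

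**The case against.** The strongest case against is that nothing here is wrong. The split is prespecified, sums to 0.05 and carries a reason: MSSA received little alpha because its higher prevalence was expected to give it ample power. Step 5 bears this out. The recycling step is also a detail that a condensed article may leave to the analysis plan. All of this stands, and it limits the point to an optional improvement.

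Two stronger readings are tempting. The first is that alpha is never recycled in this trial. The article is only silent, and the full plan is not shown, so that cannot be concluded.

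The second is that the split costs MSSA a large, known amount of power. If each test had exactly 92% power at its own level without clustering, Holm would raise MSSA power from 92% to 99%, 71% to 91% and 51% to 78% at design effects 1, 1.5 and 2. The arithmetic is right, but the premise is not in the document, which attaches its single 92% to neither test. At 0.001 and 1:1 without clustering, MSSA reaches 92% power with a reduction of only 12.8% (from 28%) to 15.8% (from 20%), whereas MRSA needs about 37% to 51%. The premise therefore requires a small MSSA effect beside a large MRSA effect, which the article nowhere states.

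One part of the case against goes too far: that clustering cuts MRSA power alongside MSSA power, so Holm can return little. That holds if both outcomes share one design effect. Step 7 shows that a common practice-level variance burdens MSSA much more. Patients are allocated through their practices (Recruitment), and the Sample size section does not exclude a cluster effect.

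**Conclusion.** The point holds as a free improvement, not as an error. The stated rule is valid but dominated: weighted Holm from the same levels keeps the 5% family-wise error and never rejects less.

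The size is open. The MSSA gain is about 0 if both strains fall by the 37% to 58% consistent with 92% MRSA power and the design effect is 1 to 2. It is at most about 5 points in the grid of equal reductions with one shared design effect. It is 9 points (71% to 80%) or 23 points (71% to 94%) in the worked case with strain-specific clustering. Reductions, admission rates, allocation, practice size, between-practice variance and independence of the two tests are all assumptions. Severity: optional.

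**What to change.** Keep the initial levels and add one sentence to the analysis plan, before outcome data are compared between groups:

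*If MRSA is significant at 0.049, MSSA is tested at 0.05; if MSSA is significant at 0.001, MRSA is tested at 0.05 (weighted Holm).*

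If the full plan already contains such a step, the sponsor need only confirm it. The change needs no further patients, data or alpha.
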